#### 9.2.2 Serious adverse events (SAEs)

A serious adverse event is any untoward medical occurrence or effect that

- results in death;
- is life threatening (at the time of the event);
- requires hospitalisation or prolongation of existing inpatients' hospitalisation;
- results in persistent or significant disability or incapacity;
- is a congenital anomaly or birth defect; or
- any other important medical event that did not result in any of the outcomes listed above due to medical or surgical intervention but could have been based upon appropriate judgement by the investigator.

An elective hospital admission will not be considered as a serious adverse event.

All events will be reported by the investigator to the sponsor. Patients will still be included in our database and will not be withdrawn from this study in case an adverse event occurs. To our knowledge, no other adverse events might occur when participating in this study.

The sponsor will report the SAEs through the web portal ToetsingOnline to the accredited METC that approved the protocol, within 7 days of first knowledge for SAEs that result in death or are life threatening followed by a period of maximum of 8 days to complete the initial preliminary report. All other SAEs will be reported within a period of maximum 15 days after the sponsor has first knowledge of the serious adverse events.

### **9.3 Follow-up of adverse events**

All AEs will be followed until they have abated, or until a stable situation has been reached. Depending on the event, follow up may require additional tests or medical procedures as indicated, and/or referral to the general physician or a medical specialist. SAEs need to be reported till end of study within the Netherlands, as defined in the protocol.

### **9.4 Data Safety Monitoring Board (DSMB) / Safety Committee**

An independent DSMB will be established. The members of the DBMS will be:

- [name]. [name], vascular surgeon, Erasmus Medical Center
- Dr. [name], epidemiologist, Amphis Hospital
- [name], scientific advisor/monitor, Amphia Hospital

None of the members are otherwise involved in the study and the members have no conflict of interest with the trial. The DSMB will assess the safety of the tested prehabilitation component during the trial. Interim analysis for the DSMB meetings shall be focused on complications. Data will be presented as a percentage.

Based on this data, the DSMB will recommend one of the following actions:

- No action needed, trial continues as planned
- Proposing protocol changes
- Early stopping due to safety concerns

The advice(s) of the DSMB will only be sent to the sponsor of the study. Should the sponsor decide not to fully implement the advice of the DSMB, the sponsor will send the advice to the review committee, including a note to substantiate why (part of) the advice of the DSMB will not be followed.

## 10. STATISTICAL ANALYSIS

Statistical analyses are performed using IBM SPSS statistical software (SPSS Inc., Chicago, Illinois, USA). A two-sided p-value of less than 0.05 will be considered statistically significant. Adjusted analysis with prognostic baseline characteristics (e.g. gender, age) will be performed using regression analysis. This analysis corrects for baseline differences, optimizes statistical power, and provides better individualized treatment effect estimates. Missing data will be studied for specific patterns of occurrence, and multiply imputed. A power analysis with sample size calculation is performed, as described in paragraph 4.4 (sample size calculation).

Results of categorical data variables are described in frequencies with percentages and differences will be tested using the Chi-square test. Continuous data are described as median (interquartile range) and Mann-Whitney U-tests will be performed to test for group differences. Ordinal variables will be tested using the Mann-Whitney U-test. Data analysis will be done according to the intention-to-treat concept, which implies that all patients are included in the analysis irrespective of whether they completed the prehabilitation program. Secondary, a per protocol analysis will be performed, although interpretability may be difficult for this analysis. All epidemiological issues and statistical methods will be discussed with [name]. [name], a member of the research group.

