### 8.2 Randomisation, blinding and treatment allocation

Randomization will be performed immediately after inclusion of a participant, either by the VNP or by the responsible researcher. Participants will be allocated to either the prehabilitation group or the control group. A variable block randomization procedure will be applied to minimize the risk of unequal group sizes and to reduce predictability of assignments. To further ensure comparability between study arms, randomization will be stratified by the participating hospital (to eliminate possible differences between hospitals). By stratifying we aim to prevent systematic imbalances and to enhance the internal validity of the trial. The randomization procedure will be carried out using the validated electronic data capture system Castor EDC. This study is not subject to blinding due to the extensive and active nature of the intervention. While blinding is not feasible, objective outcome measures and standardized assessment procedures will be used to minimize potential bias.

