### 10.2 Secondary study parameter(s)

As described in chapter 8.1 secondary study parameters will be postoperative complications, hospital readmission rate, 6-month mortality, the QoL of both patient and their informal caregiver (measured by using the WHOQoL-BREF), health related QoL of patients (measured using the EQ-5D-5L), burden on IC (using the CSI), the level of perceived SDM of the patient and their IC (using the CollaboRATE), perceived and preferred roles in DM of the patient and their IC (using the ACPS) and preferred participation in SDM of the patient and their IC (using the PICS). Continuous outcomes are analyzed using a linear regression model, whereas binary outcomes are analyzed by using a logistic regression model. Correction for important covariates (such as age,

gender, surgical history, comorbidities, use of medication, smoking status, use of alcohol, home situation) will take place. Hospital site will be a factor in the regression analysis. Repeated measures will be analyzed with mixed effect models with random effects per patients to address within patient clustering.

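### The only method named for ordinal outcomes is an unstratified Mann-Whitney test, which cannot carry the hospital and covariate correction promised in section 10.2

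*Protocol*

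**What the plan says.** Three parts of the protocol bear on this.

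- **Section 10 (general rules).** For ordinal data: "Ordinal variables will be tested using the Mann-Whitney U-test". No stratification or covariates are attached. The same section sets the significance level ("A two-sided p-value of less than 0.05 will be considered statistically significant"), says "Missing data will be studied for specific patterns of occurrence, and multiply imputed", and adds in general terms: "Adjusted analysis with prognostic baseline characteristics (e.g. gender, age) will be performed using regression analysis".
- **Section 8.2.** The design uses variable blocks, and "randomization will be stratified by the participating hospital".
- **Section 10.2 (secondary outcomes).** The list includes "perceived and preferred roles in DM of the patient and their IC (using the ACPS"). The models follow: "Continuous outcomes are analyzed using a linear regression model, whereas binary outcomes are analyzed by using a logistic regression model". Covariate correction is promised, and then: "Hospital site will be a factor in the regression analysis. Repeated measures will be analyzed with mixed effect models".

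Neither ordinal regression nor a stratified rank test appears anywhere in the protocol.

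**The concern.** Continuous and binary outcomes get a simple test in section 10 and an adjusted model with hospital in section 10.2. Ordinal outcomes get the simple test and no named model. An analyst who follows section 10 literally would compare arms on an ordinal outcome without regard to the factor used to stratify randomisation, and could not deliver the correction that section 10.2 promises.

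Three things are at stake, all for secondary outcomes:

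1. When arms are balanced within hospitals and hospitals differ on the outcome, a test that ignores hospital counts between-hospital spread as noise. It becomes conservative and loses some power.
2. A test alone reports no size of effect.
3. Multiple imputation needs an estimate and a standard error from each completed data set, and the protocol does not say what these are for an ordinal outcome.

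The trial is not blinded. Leaving open the choice between a linear model, a dichotomised logistic model and an ordinal model is therefore best avoided.

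**Working it through.** **Step 1. Does any stated model cover an ordinal outcome with hospital in it?**

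| Outcome type | Simple test (section 10) | Model with hospital (10.1, 10.2) |
|---|---|---|
| Continuous | Mann-Whitney | linear regression |
| Binary | chi-square | logistic regression |
| Ordinal | Mann-Whitney | none named |
| Repeated measures | – | mixed model |

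The mixed model does not fill the gap for the ACPS, which is collected once, after the second outpatient visit (sections 3 and 8.3).

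**Step 2. The plan's own figures.** Section 4.4 gives power for length of stay and complications only, so there is no ordinal figure to reproduce. As a check on the design inputs, power for a length-of-stay ratio of 0.75 with SD of log(LOS) 0.9 and 150 per arm is Φ(|ln 0.75| × √(150/2) / 0.9 − 1.96) = Φ(2.768 − 1.960) = 79.1%. The protocol states 80%, so this agrees.

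**Step 3. Size of the effect by simulation.** From the protocol: 300 patients, 100 per hospital, three hospitals, two-sided 5%. Assumed: 50:50 allocation within hospital, five categories with shares 10/25/35/20/10%, proportional odds, treatment odds ratio 1.8, and hospital effects of −a, 0 and +a on the log-odds scale. The SD of these three effects is a × √(2/3), so a = SD × √1.5. Each setting has 4,000 simulated trials. The plain test is a tie-corrected Mann-Whitney and the stratified test is van Elteren by hospital.

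| Hospital SD | Odds ratio, neighbouring hospitals (exp a) | Odds ratio, outer hospitals (exp 2a) | Type I error, plain / stratified | Power, plain / stratified |
|---|---|---|---|---|
| 0 | 1.0 | 1.0 | 4.9% / 5.0% | 79.4% / 79.1% |
| 0.25 | 1.36 | 1.84 | 5.0% / 5.3% | 80.1% / 80.5% |
| 0.5 | 1.84 | 3.40 | 4.3% / 5.2% | 78.1% / 80.4% |
| 1.0 | 3.40 | 11.6 | 2.4% / 4.5% | 69.8% / 80.3% |

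The Monte Carlo standard error is √(0.05 × 0.95 / 4000) = 0.3 points for type I error and √(0.8 × 0.2 / 4000) = 0.6 points for power.

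A separate run of 6,000 trials per setting (log odds ratio 0.6, neighbouring hospitals 0.5, 0.8 or 1.0 apart in log odds) gave the plain test type I error of 4.2%, 3.5% and 3.0% and power of 81%, 78% and 75%. The stratified test had type I error of about 5% and power of 82%, 82% and 83%.

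**Step 4. Analytic check.** Let ρ be the share of outcome variance that lies between hospitals. On the latent logistic scale, ρ ≈ SD² / (SD² + π²/3). Balanced strata remove that share from the true variance of the arm comparison, but the plain test still charges for it. Its effective critical value is therefore 1.96 / √(1 − ρ). Taking 80% power for the stratified test (2.80 = 1.96 + 0.84):

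- SD 0.5: ρ = 0.25 / 3.54 = 7.1%; critical value 2.03; type I error 4.2%; power Φ(2.80 − 2.03) = 78%.
- SD 1.0: ρ = 1 / 4.29 = 23.3%; critical value 2.24; type I error 2.5%; power Φ(2.80 − 2.24) = 71%.

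Both agree closely with the simulation.

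**Step 5. Can a Mann-Whitney result be pooled?** The test's p-value has no estimate and standard error. The associated probability index (the chance that a patient in one arm scores higher than one in the other, ties counted half) has both. With 150 per arm, no hospital effect, 20% missing, 20 imputations and 1,500 simulated trials, pooling that index by Rubin's rules gave type I error of 5.5% and power of 72% at odds ratio 1.8. Pooling is thus possible, but the protocol does not name the quantity to pool.

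**The case against.** The case against is substantial and trims the point.

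- **The section 10 tests may be only an unadjusted layer.** Continuous and binary outcomes also get simple tests there and regression later. The sentence "Adjusted analysis with prognostic baseline characteristics (e.g. gender, age) will be performed using regression analysis" is not limited by type of variable. This stands in part: a reader should not infer that the protocol rules out adjusted analysis of ordinal outcomes. It still names no model that fits them, and the one rule it does state for them cannot carry hospital.
- **The detail belongs in the SAP.** A silent protocol would be no finding. This one fixes a test that does not fit the promise in its own section 10.2, so the two need to be reconciled.
- **The ACPS is not stated to be ordinal.** Correct. Its scoring is in an attachment that is not shown. That it is ordinal is an inference, and the point applies to whichever secondary outcomes are scored that way.
- **Imputation.** One might infer that a Mann-Whitney analysis leaves nothing that can be pooled. That is too strong, since the probability index pools adequately. Only the lack of a specified estimate remains.
- **Power.** One might infer that power is certainly lost. The protocol gives no between-hospital difference on any ordinal outcome, and the loss is nil to negligible when hospitals differ little. The 10-point loss needs an odds ratio of 11.6 between the outer hospitals.
- **Validity.** The error is in the conservative direction. The outcomes are secondary, and no power is claimed for them.

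**Conclusion.** The point holds as a mismatch between sections 8.2, 10 and 10.2: the stated ordinal test ignores the stratification factor, and section 10.2 gives no means of applying the correction it promises to an ordinal outcome. It is of minor weight.

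Under the assumed five categories and treatment odds ratio of 1.8, the cost in power is nothing to about 2 points for small to moderate hospital differences (SD 0 to 0.5 in log odds) and about 10 points for a very large one (SD 1.0). Some hospital difference is plausible, because the programme is already standard care at one hospital and still to be introduced at the other two, but its size is unknown.

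The documents do not support reading this as a false-positive risk, because the plain test stayed at or below 5% in every setting. Nor do they support reading it as a flaw in the primary analysis: section 10.1 includes hospital as a factor for length of stay.

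**What to change.** Replace the ordinal sentence in section 10 with wording such as: *Ordinal outcomes will be analysed by proportional-odds logistic regression with arm, hospital and the covariates of section 10.2. The common odds ratio with its 95% confidence interval will be reported, pooled over imputations by Rubin's rules.* Name the same model in section 10.2 beside the linear and logistic models, and state which secondary outcomes are treated as ordinal.

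If an unadjusted rank test is kept beside the model, stratify it by hospital (van Elteren). It should not replace the model, because it takes no covariates beyond the stratum and gives no estimate to pool.

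The cost is a sentence or two of text. No new data or patients are needed, and the model is standard software output. The small downside is that the proportional-odds assumption has to be checked. Where hospitals do not differ, stratifying costs essentially nothing (79.1% against 79.4% power, within simulation error).

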### 10.1 Primary study parameter(s)

Primary endpoint of the study is the LOS. LOS will be extracted from the electronic patient dossiers (EPD). We will use a linear regression model for important covariates (such as age, gender, surgical history, comorbidities, use of medication, smoking status, use of alcohol, home situation) that may contribute to the outcome of LOS. We expect the continuous variable LOS to be skewed, therefore we will perform a log-transformation. Hospital site will be a factor in the regression analysis. This way stratification will take place for each hospital site.

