### 3. STUDY DESIGN

An RCT with a cost-effectiveness analysis, will be performed in three non-university large teaching hospitals in the Netherlands (Amphia Hospital Breda, Elisabeth Tweesteden Hospital Tilburg and Meander Medical Center Amersfoort), during the period of November 2025 to May 2028. All patients of 65 years or older, with a new onset of CLTI presented at the outpatient clinic of the vascular surgeon, who are planned for surgical or endovascular revascularization and who meet the in- and exclusion criteria are asked to participate in the study. In addition, their primary IC will also be requested to take part in the study. A primary IC is defined as follows: the person most involved in caring for the CLTI patient and supporting at least one instrumental activity of daily living of the patient or defined as the contact who supports in decisions by the patient. Patients can still be included, if their primary IC refuses participation. However, primary ICs can only be included together with a patient.

At the outpatient clinic information about the POCI-study is provided by a VNP or researcher and patients and ICs receive an information folder. They are called by telephone the next day by a researcher or VNP to ask if they want to participate. If so, oral informed consent will be obtained by the researcher or VNP and patients are randomized immediately upon inclusion, either into the prehabilitation group or the control group, the latter receiving the standard of care. Their IC will automatically be randomized to the same group. Within a few days all patients undergo a general health screening by a VNP or researcher and a blood sample will be taken as part of the standard care. Written informed consent will be obtained during this visit. Afterwards patients receive three questionnaires: the WHOQoL-BREF, the EQ-5D-5L and the iMTA Medical Consumption Questionnaire (iMCQ) (t=0). ICs are also asked to fill in two questionnaires: the WHOQoL-BREF, and the CSI (t=0). Afterwards, patients randomized into the intervention group are referred to the prehabilitation program where they are assessed by a physiotherapist and if indicated also a geriatrician, dietician or a quit smoking coach. The prehabilitation program will take two weeks, considering both the time needed to possibly reach significant results with the program and the time in which treatment is planned and must take place.

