## 4. STUDY POPULATION

### 4.1 Population (base)

All patients in the Amphia Hospital (Breda), the Elisabeth Tweesteden Hospital (Tilburg) and the Meander Medical center (Amersfoort), referred by a general practitioner with suspected CLTI, will be seen on the outpatient clinic by a vascular surgeon. Diagnosis of CLTI is based on impaired perfusion combined with a Rutherford classification of either stage 4 or 5 (8). The severity of the CLTI is scored by the vascular surgeon by using the Wifl score (9). All CLTI patients exceeding the age of 65 with a Wifl-score of Wounds (W)  $\leq 2$  and foot infections (fi)  $\leq 2$  are screened for eligibility according to the in- and exclusion criteria stated below. Additional imaging is requested. If eligible, patients are offered the study information and asked to participate in this study. Their primary IC will be asked to participate with the patient.

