#### 4.4 Sample size calculation

In this multicenter study we aim for a total of 300 patients, 100 patients from each hospital. With this sample size we have 80% statistical power to test hypotheses with 2-sided alpha set at 5% for the following differences between randomized groups.

Length of hospital stay: The calculation of the effect size is based on the difference in means with SD. In a previous study (7), prehabilitation was associated with a difference of 2 vs over 4 days on average. A halving in length of stay requires 54 patients in total (27 per group, assuming a SD of log (LOS) of 0.9, as in the previous study). With 300 patients, a decrease by a factor 0.75 (so 25% reduction in LOS) provides 80% power.

For complications, we will analyze minor and major complications. In the previous study (7), prehabilitation was associated with the following reductions in complications: minor, 26 vs 14%; major 23 vs 18%. These differences would require sample sizes of 346 and over 2000 patients in total respectively. With 300 patients we will have reasonable power for detecting a difference in minor complications (power 69%), but insufficient statistical power for a difference of 23 vs 18% in major complications (power 15%). These calculations were done using the online sample size calculators at <https://sample-size.net/>

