#### First visit to the outpatient clinic of the vascular surgeon (diagnosis)

All patients will be examined by the vascular surgeon at the first outpatient clinic visit. The WIfI score will be used to classify the patient at the time of initial presentation (see Appendix 2-Meetinstrumenten). This score for threatened lower limbs combines the three main factors that have an impact on limb amputation risk: Wound (W), Infection (I) and foot Infection (fI) (9). This score is helpful in estimating the benefit of revascularization and the risk of amputation at one year for each individual patient.

Additional research will be requested. This may include an Electrocardiogram (ECG), Ankle-Brachial Index (ABI), toe pressure in case of non-compressible vessels (common in diabetics). Imaging may be performed by duplex, or Magnetic Resonance Angiography (MRA) or Computed Tomography Angiogram (CTA). Vascular pathology will be scored using the Trans-Atlantic Inter-Society Consensus Document on Management of Peripheral Arterial Disease II (TASC-II, see Appendix 2-Meetinstrumenten) and description of the crural outflow (in 1,2 or 3 arteries) (10-12).

All patients meeting the inclusion criteria for this study and their IC receive an information map, consisting of an (patient) information folder (PIF) and an Informed consent form and are called the next day by a researcher or VNP to ask if they want to participate in the study (E1.Proefpersonen informatiebrief and E1.Mantelzorger informatiebrief).

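### The covariates named for the length-of-stay model include no limb-severity measure, although Rutherford stage and WIfI are known before randomisation; naming them costs nothing and may gain a little precision

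*Protocol*

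**What the plan says.** **Model.** Protocol section 10.1 analyses length of stay (LOS) by linear regression after log-transformation, with hospital as a factor and "important covariates (such as age, gender, surgical history, comorbidities, use of medication, smoking status, use of alcohol, home situation". Section 10.2 gives the same eight items for the secondary outcomes. Section 10 states the purpose more generally: adjustment is for prognostic baseline characteristics, with age and gender as examples, and is meant both to correct baseline differences and to improve power.

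**Severity.** Rutherford stage 4 or 5 is part of the diagnosis and of the inclusion criteria (sections 4.1 and 4.2). Section 8.3, on the first outpatient visit, adds: "The WIfI score will be used to classify the patient at the time of initial presentation".

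**Order of events.** Patients are telephoned the day after that visit and, if they consent, "patients are randomized immediately upon inclusion" (section 3). The health screening at the MVE follows within a few days, in both arms, before the intervention arm is referred to the programme. Section 8.2 stratifies randomisation by hospital and by nothing else.

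**Sample size.** Section 4.4 takes "27 per group, assuming a SD of log (LOS) of 0.9, as in the previous study" for a halving of LOS, and then states: "With 300 patients, a decrease by a factor 0.75 (so 25% reduction in LOS) provides 80% power".

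**The concern.** The named covariates cover demographics, history, lifestyle and home situation, but not the severity of the disease being treated. Rutherford stage and WIfI are the two measures certain to be on file for every patient before allocation, and neither is named in 10.1 or 10.2.

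The protocol itself treats severity as clinically important. A wound or foot-infection grade of 3 defines the need for urgent treatment (4.3), WIfI is used to estimate amputation risk and benefit of revascularisation (8.3), and either treatment route may include debridement and minor amputation (8.3). It is reasonable to expect, though the document does not show it, that severity also bears on LOS.

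Two things are at stake, both modest. A covariate that predicts log LOS reduces the residual variance and so raises power for the primary comparison. And because only hospital is balanced by design, regression is the only means of correcting a chance difference in severity between arms.

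**Working it through.** **Inputs.** From section 4.4: two-sided alpha 0.05, 300 patients, SD of log LOS 0.9, LOS ratio 0.75. Equal allocation, 150 per arm, is assumed. The effect on the log scale is |ln 0.75| = 0.2877.

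**Step 1: reproduce the plan's figures.**
- Patients per arm = 2 × (1.960 + 0.842)² × 0.9² / effect².
- For a halving, effect = ln 2 = 0.693: 27 per arm, 54 in total, as stated.
- For a ratio of 0.75: 154 per arm, 308 in total, within 3% of the planned 300.
- Power at 150 per arm: SE = 0.9 × √(2/150) = 0.1039; 0.2877/0.1039 = 2.768; power = Φ(2.768 − 1.960) = 79.1%.

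The stated 80% therefore holds to rounding with the unadjusted SD. It takes no credit for any covariate.

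**Step 2: add severity.** If severity explains a further share R² of the variance of log LOS, the residual SD becomes 0.9 × √(1 − R²). The document gives no R², so these values are assumptions.

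| Assumed extra R² | Residual SD | Power, 300 patients | Total for 80% power |
|---|---|---|---|
| 0 | 0.900 | 79.1% | 308 |
| 0.02 | 0.891 | 79.9% | 302 |
| 0.05 | 0.877 | 81.1% | 292 |
| 0.10 | 0.854 | 83.1% | 278 |
| 0.20 | 0.805 | 87.2% | 246 |

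**Step 3: does the starting point matter?** The first row credits the covariates already planned with nothing. If they explained 10% of the variance, power would start at 83.1%. A further 5% for severity (R² 0.15 in all) would bring it to 85.1%. The gain is again about 2 points per 0.05 of R². The starting point changes the level of power, hardly the increment. What counts is how much severity adds beyond the other covariates, and that is unknown.

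**Step 4: which R² is plausible? (illustration, all inputs assumed)** Suppose half the patients are Rutherford 5 and stay 1.5 times as long. Then R² = 0.5 × 0.5 × (ln 1.5)² / 0.81 = 0.05. That is severity's share taken alone; overlap with the planned covariates would lower it.

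**Step 5: chance imbalance (same illustration).** The SE of the between-arm difference in the proportion with Rutherford 5 is √(0.25 × 2/150) = 0.058. A difference of 10 percentage points or more then has a probability of about 8%. A 10-point difference would shift an estimate not adjusted for severity by 0.10 × ln 1.5 = 0.041 on the log scale, or 0.041/0.288 = 14% of the target effect.

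**The case against.** The strongest reply is that nothing has been left out. The list in 10.1 and 10.2 is introduced by *such as*, section 10 commits to prognostic baseline characteristics in general, and the final covariate set may be fixed in a statistical analysis plan that is not at hand. This stands: severity is not excluded, and a missing final list is not in itself a fault of the protocol. What remains is narrower. The protocol chose to name eight items, twice, and the severity of the index disease is not among them.

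Three stronger readings are tempting, and the document supports none of them.

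- *Precision is certainly lost.* A reader might infer this from the list. It would be true only if severity were left out of the final model and predicted LOS beyond the other covariates. Section 8.3 links WIfI to amputation risk and benefit of revascularisation, not to LOS. Eligibility also narrows the range to Rutherford 4 or 5, with wound and foot-infection grades of at most 2.
- *The trial is underpowered without severity.* It is not. The planned power reproduces with no covariate gain.
- *Covariates recorded after randomisation bias the primary analysis.* The MVE screening is the same in both arms and comes before the programme starts, and smoking, alcohol, medication and home situation describe pre-existing status. The programme cannot yet have changed them. What is left is a small risk that unblinded staff record them differently by arm, or that they are missing for patients who drop out before the screening. Neither costs precision in the sense discussed here.

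A swap would also be a mistake. Removing comorbidities or surgical history to make room for severity could lose more than it gains; the multidisciplinary meeting (8.3) takes comorbidity into account when choosing the treatment.

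**Conclusion.** The point holds as a modest improvement, not as an error or contradiction. The covariates named in 10.1 and 10.2 omit limb severity, although it is scored for all patients before randomisation, is not a stratification factor, and fits the purpose that section 10 gives for adjustment. A model restricted to the named items may lose some precision and would leave a chance imbalance in severity uncorrected.

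The gain is probably small: about 1, 2 or 4 percentage points of power at an assumed extra R² of 0.02, 0.05 or 0.10. These values do not come from the document, and they must be read as what severity adds beyond the covariates already planned. The sample size in section 4.4 is unaffected.

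**What to change.** In sections 10.1 and 10.2:

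- Add first-visit severity to the named primary covariates, as Rutherford stage (4 vs 5), WIfI grades, or both. Stage 5 is defined by tissue loss and so overlaps with the wound grade. If both are entered, choose the coding in advance with that in mind.
- Keep hospital, age, sex, comorbidities and surgical history in the primary model.
- Define smoking, alcohol, medication and home situation by their status before randomisation, so that values recorded later at the MVE still refer to that time.
- State that procedure type is not a covariate, because it is decided after randomisation and partly on the MVE findings.

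The cost is a few more model terms and some wording. All the variables are already collected.
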